### Randomization

Twenty-six pairs of matched clusters have been ranked from the top best matched to the bottom matched based on matching criteria. Within each pair, the random allocation rule has been used to assign either to the intervention group or control group (Additional file 1). There is no blinding of the researchers and participants in the study due to the nature of the intervention and ethical reasons. Data collectors during follow-up will be blinded to allocation.

### Potential contamination

Most of the clusters are geographically separated and that the distance between clusters are at least 500 m from each other which may prevent the possible treatment contamination between intervention and control arms. There may be potential contamination due to sharing of training knowledge but knowledge is not equal to implementation, moreover, the control group FCHVs will not be followed-up by our FRAs. The likely contamination of text messaging through mobile phone to the pregnant women will be confirmed by asking whether they received MCH information from the intervention area during follow-up period.

### Interventions

The intervention has been implemented by two approaches; i) Capacity building of FCHVs (reinforcement training on maternal and new-born health followed by regular supervision) for the promotion of health seeking behaviour among pregnant women, and ii) periodic text messaging to the pregnant women through a mobile phone for demand generation of MCH services.

#### Capacity building of FCHVs

##### Reinforcement training

FCHVs have received one-day extensive orientation/reinforcement training to equip with the knowledge and skills of MCH services. The content of the reinforcement training to FCHVs comprised of three packages; maternal and neonatal health (MNH) counselling package “Jeevan Suraksha” also called “birth preparedness package” developed by USAID; nutrition training package developed by ministry of health/micronutrient initiative, Nepal [27]; and “Bal Parivar Mitra” also called “baby friendly family”, a module for community-based maternal and child health nutrition (CB-MCHN) project [28].We provided daily allowance and refreshment to FCHVs during training course. FCHVs who have attended the training and actively involved throughout training day. We have conducted pre- & post-test of the trainees (FCHVs) and found good improvement in their knowledge regarding training course.

##### Supervision and monitoring

A monthly visit to FCHVs in the intervention areas will be made by researchers using supervision and monitoring format adopted from “Bal Parivar Mitra” monitoring format for the CB-MCHN project (motivation for change) in India [28]. The FCHVs will be assessed by researchers against their performance on MCH services delivery (Additional file 2).

#### Text messaging through a mobile phone

A short text message will be sent regularly through a mobile short messaging service (SMS) system to either pregnant woman or her family member (who can convey messages to the participant) in the intervention arm. The start point of sending text message is on the individual basis and the process starts immediately after participants got recruited and allocated in the study. Participants in this arm will be provided with a diary and a pencil and will be advised to note down messages received by them. Text messages will be either in Nepali or in Maithili version based on participant’s language preference. The frequency will be one message every fortnight between 4th and 6th months and every week thereafter till delivery of the baby. The enquiry will be made within a week after the expected date of delivery (EDD) for the outcome of pregnancy by research assistants. One message per week will be sent during the postnatal period (up to five months after delivery). The content of SMS is about dates of ANC / PNC visit, care during pregnancy, danger signs in pregnancy, postnatal care and care of new born baby including breastfeeding.

A package of common messages of 160 or fewer letters has been prepared for all participants in the intervention arm according to the stage of pregnancy and the postnatal period, focussing on routine antenatal care, place of delivery, postnatal care and diversified dietary intake including how frequently they consume such diet. All together 5 ‘message packages’ were created and each package contained 5 relevant information (Additional file 3). All the messages have been created according to stage of the pregnancy and postpartum period adopted from the training materials for “Jeevan Suraksha” (Additional file 4), Micronutrient Initiative-Nepal and motivation for change from CB-MCHN project [27, 28]. The timing of text messaging will be either 6:00–9:00 AM or 6.00–9:00 PM as participants are generally free during this period.

Both the intervention and control groups will receive regular antenatal and postnatal care provided by the government through local health facilities. These services are free of cost at the point of delivery. Both intervention and control arms participants should make at least four ANC visits (first within 4 months, second within 6 months, third within 8 months and fourth within 9 months, respectively in nearby health facility) and three home visits (First visit at day one, second at day 3 and third at day 7) in the first 7 days after childbirth by FCHVs/CHWs as part of postnatal care service.

**Usual care:** FCHVs in the control clusters will not receive training on the MCH service package and participants (pregnant women) also will not receive any text message during study period. There will be no supervision to the FCHVs from the project side, but the monthly visit by MCHWs/CHWs to them has been made from the government side as part of regular supervision to collect integrated community health service reports including MCH service reports. Any adverse event.

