### Study population

The study population consists of pregnant women aged between 15 and 49 years in their second trimester (gestation period between 13 and28 weeks). Pregnancy status was confirmed by a validated pregnancy test report. The gestational age will be determined based on first date of last menstrual period by asking with the participant. The expected date of delivery (EDD) based on gestational age will be confirmed through physical examination of pregnant women by nursing staff. Women were excluded if they had the following characteristics: (a) those not planning to stay at the study site during pregnancy and postpartum, (b) any physical and mental disability (which can adversely influence the study results), (c) women who have miscarriage or still birth during recruitment process, and (d) woman who are not willing (to give consent) to participate in the study.

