### Study design

This is a two-parallel arms **cluster RCT** in rural community settings, provided participants are eligible for the study. Participants are recruited from 52 study areas by research assistants with the help of FCHVs. Then participants are then randomly assigned into intervention group and control arms based on clusters with approximately equal number of participations in each group.

Baseline information is collected after allocation of the clusters in two groups. At the same time, one-day extensive reinforcement training to the FCHVs in the intervention arm is conducted. Intervention group will receive text messages in their mobile phones. The principal investigator is responsible for sending text messages to the participants once they are recruited in the study and this process will continue until the fifth-month after childbirth. There will be three assessments during follow-up period and the data will be collected during these assessment periods: between 38 and 39 weeks of gestation, during delivery, and at 7 months after child birth. During the follow-up period, monitoring and supervision of FCHVs in the intervention arm will also be done to assess their performance. Additionally, assessment of child will be carried out at birth and 7 months after birth [Fig. 1].

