### Identification and recruitment of participants

All households with pregnant women in 52 clusters have been identified and screened applying inclusion and exclusion criteria. The identification of pregnant women has been made with the help of FCHVs’ antenatal registers. Pregnant women from each household in have been registered by FCHVs in their respective ward. All pregnant women with gestational period between 13 to 28 weeks are included in the study. Each household is coded and marked in the outside wall with a visible unique serial number to track participants during follow-up period.

The baseline information of these pregnant women was collected between July and September 2015. Selection of participants has been done by trained female research assistants (FRA), who are fluent in both Nepali and Maithili languages. Written informed consent have been taken from each participant who are willing to participate in the study. Participants are informed about the purpose of the study, advantages and any potential harms arising from a study. Head of the family, usually husband or close relatives of the relevant participants, were also informed about the study. For any adverse event or inquiry by the participants will be entertained or clarified.

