### Outcome measures

#### Primary and secondary outcomes of the study include;

Primary OutcomesUtilization of Skilled Birth Attendant (SBA) by pregnant women during delivery.Consumption of diversified diet by women during pregnancy and postpartum.

Secondary OutcomesFour ANC visits by pregnant womanDelivery of baby in a birthing centre (health care facility)PNC visits by mother and childWeight gain, haemoglobin changes and increase in uterine height of woman during pregnancyChanges in child feeding practices among mothers, andPerformance of FCHVs

Details of outcome measures are given in Additional file 5.

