### Research instruments

Structured and semi-structured questionnaires were adapted from NDHS 2011 to collect quantitative information [4]. There are three sections in a questionnaire: i) baseline questionnaire ii) antenatal follow-up questionnaire, and iii) postnatal follow-up questionnaire. The baseline questionnaire includes three components: i) socioeconomic information, ii) obstetric/gynaecologic history, anthropometric measurement and existing service utilization of pregnant women, and iii) Food Frequency Questionnaire (FFQ) and dietary diversity questionnaire recommended by the UN Food and Agriculture Organisation [29]. The antenatal follow-up questionnaire also consists of three components: i) information on services utilization, ii) anthropometric measurement and iii) FFQ and dietary diversity questionnaire. Postnatal follow-up questionnaire consists of two components i) maternal and neonatal services utilization along with morbidity and mortality and ii) new-born anthropometric measurement and child care practices. A focus group discussion (FGD) guide is prepared to collect information on attitudes and beliefs of FCHVs and pregnant women on service utilization and nutrition practices to give an in-depth understanding on the status of dietary diversity and complement some of the quantitative findings.

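### The secondary outcome of four ANC visits partly reflects visits made or missed before enrolment, so its analysis should adjust for earlier visits and for gestational age at entry

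*Protocol article*

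**What the plan says.** Four statements in the protocol article set the timing.

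- **Entry.** Study population defines eligibility as "pregnant women aged between 15 and 49 years in their second trimester (gestation period between 13 and28 weeks". Identification and recruitment of participants repeats it: "All pregnant women with gestational period between 13 to 28 weeks are included in the study".
- **Start of the intervention.** For the messages, the section on text messaging says that "the process starts immediately after participants got recruited and allocated in the study". For the health volunteers (FCHVs), Study design describes the baseline data collection and continues: "At the same time, one-day extensive reinforcement training to the FCHVs in the intervention arm is conducted".
- **Visit schedule.** The usual-care text at the end of the text messaging section expects, in both arms, "four ANC visits (first within 4 months, second within 6 months, third within 8 months and fourth within 9 months".
- **Outcome.** Outcome measures names four ANC visits first among the secondary outcomes, gives no timing or counting rule, and adds: "Details of outcome measures are given in Additional file 5".

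On analysis, Data management and analysis plan assigns primary and secondary outcomes to logistic regression with odds ratios. The only outcomes for which it names confounder adjustment are weight gain and haemoglobin. Research instruments lists among the baseline items "anthropometric measurement and existing service utilization of pregnant women".

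**The concern.** The window for entry overlaps the limits for the first two visits. For a woman enrolled at 20 weeks, whether the first visit was on time is already settled. For a woman enrolled at 27 or 28 weeks, the same is true of the first two. The intervention can act only on what comes later, yet the outcome is a total of four.

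Two things are at stake.

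- **Sensitivity.** Part of the variation in the outcome comes from behaviour before the intervention, so a real effect on later attendance shows up less clearly. ANC attendance is part of the stated hypothesis, so a weak result here would be read as evidence.
- **Comparability of the arms.** Baseline information is collected after the clusters have been allocated (Study design), researchers and participants are not blinded (Randomization), and FCHVs help to identify and register women. If one arm enrols women later in pregnancy, or with more visits already made, that difference enters an unadjusted odds ratio directly.

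**Working it through.** **1. The plan's own figure.** The stated sample size rests on skilled birth attendance, not on ANC. With 12% versus 32%, two-sided 0.05, power 0.80 and unpooled variance:

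(1.960 + 0.842)² × (0.12 × 0.88 + 0.32 × 0.68) / 0.20² = 63.4, rounded up to 64 per arm.

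64 × 2.29 = 146.6, so 147. Then 147 × 1.2 = 176.4, so 177 per arm and 354 in total. The figures reproduce, and nothing below changes them.

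**2. Share of women enrolled after each limit.**

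- From the article: entry from 13 to 28 weeks; visits due within 4, 6, 8 and 9 months.
- Assumed: gestational age at entry is uniform over 13 to 28 weeks. A month is read either as 4 weeks or as a calendar month (365.25 / 12 / 7 = 4.35 weeks).
- Formula: share past a limit of L weeks = (28 − L) / 15, set to zero when L exceeds 28.

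| Visit | Limit, weeks (4-week / calendar month) | Share enrolled after the limit |
|---|---|---|
| 1 | 16 / 17.4 | 12/15 = 80% / 10.6/15 = 71% |
| 2 | 24 / 26.1 | 4/15 = 27% / 1.9/15 = 13% |
| 3 | 32 / 34.8 | 0% |
| 4 | 36 / 39.1 | 0% |

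**3. Share of scheduled visits due before enrolment.**

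- 4-week months: 0.80 + 0.267 = 1.07 visits per woman; 1.07 / 4 = 27%.
- Calendar months: 0.707 + 0.127 = 0.83 visits per woman; 0.83 / 4 = 21%.

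Counting the whole of week 28 as eligible (range 13 to 29) changes little: 73% to 81% for the first visit, 18% to 31% for the second, and 23% to 28% of all four.

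**4. What this does to the effect.** The answer depends on the counting rule.

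- *Visits must be on schedule.* A woman who missed a visit already due has failed at entry. Let f1 and f2 be the shares past limits 1 and 2, and m an assumed probability of missing each visit already due. The share that has failed at entry is (f1 − f2) × m + f2 × [1 − (1 − m)²].
  - m = 10%, calendar months: 0.58 × 0.10 + 0.127 × 0.19 = 8%.
  - m = 50%, 4-week months: 0.533 × 0.50 + 0.267 × 0.75 = 47%.
  - If an assumed 20-point effect applies only to women who have not already failed, it becomes 20 × (1 − 0.082) = 18.4 points or 20 × (1 − 0.467) = 10.7 points.
- *Any four visits count.* Visits made before enrolment are credited, and late starters can still reach four. The dilution is smaller, and the article gives nothing from which to size it.

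The article gives no value for m and does not say which rule applies. The range in this step is therefore an illustration, not an estimate.

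**The case against.** The strongest case against the point is that the outcome definition is not on view. The schedule describes care that both arms should receive and is not stated as the outcome rule, and Additional file 5 may settle the matter. This stands, and it is why no size can be put on the dilution. It does not remove the overlap: for most women fewer than four scheduled visits fall due after entry, so a total of four will usually draw on earlier visits under either rule.

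A reader might infer that much of the outcome is fixed before the intervention begins, or that a stated large share of women cannot achieve it. The documents do not support either reading. The third and fourth visits fall due after entry for every eligible woman, so passed limits never settle success. Only failure can be settled, and only under the on-schedule rule. Any share of women who cannot succeed needs a missed-visit rate that the article does not give. Women were identified with the help of antenatal registers, so some may already have been in contact with services.

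A reader might also call this bias. Clusters were randomised within matched pairs after all households were enumerated, so earlier visits are balanced in expectation. Four-visit completion among women enrolled in the second trimester is a legitimate quantity, and the Background uses the same indicator nationally. What remains is lower sensitivity, together with exposure to chance imbalance or imbalance arising at recruitment.

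Finally, the adjustment list is worded openly and may be extended in an analysis plan. That is fair. The point is a recommendation about what to include, not a charge of omission.

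**Conclusion.** The point holds in limited form. The stated eligibility and the stated visit schedule mean that the four-visit outcome partly records behaviour before enrolment. If entry gestation is uniform, 71% to 80% of women enrol after the first limit and 13% to 27% after the second, so about 21% to 27% of the scheduled visits fall due before the intervention can act. The range reflects the two readings of a month.

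The consequence is a less sensitive ANC comparison, in which arm differences in entry gestation or earlier visits can move the odds ratio. The extent depends on the counting rule. One secondary outcome is affected; both primary outcomes and the sample size of 354 stand.

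**What to change.** Keep four ANC visits as the outcome and state the counting rule beside it. In its logistic regression, adjust for:

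- the number of ANC visits already made at baseline, taken from the service utilization items (Research instruments; Data collection plan);
- gestational age at enrolment (Study population).

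As a supporting analysis, report the number of ANC visits made after enrolment by arm, also adjusted for gestational age at entry because later entrants have less time left.

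Two checks come first. The article does not say that the baseline items record a visit count, so confirm that they do. Training ran alongside baseline collection, so also confirm that the count covers only visits made before the intervention reached the woman's cluster.

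Replacing the outcome with the third and fourth visits is not recommended. A visit with a later limit may still have been made before enrolment, and a woman with no earlier visits would still need four in all to have a fourth.

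The cost is two covariates and a little more analysis, with no new data if the baseline items hold the count. Trial status describes the trial as completed, so if results have already been seen, label the added analyses as such and show the unadjusted odds ratio alongside.

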### Outcome measures

#### Primary and secondary outcomes of the study include;

Primary OutcomesUtilization of Skilled Birth Attendant (SBA) by pregnant women during delivery.Consumption of diversified diet by women during pregnancy and postpartum.

Secondary OutcomesFour ANC visits by pregnant womanDelivery of baby in a birthing centre (health care facility)PNC visits by mother and childWeight gain, haemoglobin changes and increase in uterine height of woman during pregnancyChanges in child feeding practices among mothers, andPerformance of FCHVs

Details of outcome measures are given in Additional file 5.

### Research instruments

Structured and semi-structured questionnaires were adapted from NDHS 2011 to collect quantitative information [4]. There are three sections in a questionnaire: i) baseline questionnaire ii) antenatal follow-up questionnaire, and iii) postnatal follow-up questionnaire. The baseline questionnaire includes three components: i) socioeconomic information, ii) obstetric/gynaecologic history, anthropometric measurement and existing service utilization of pregnant women, and iii) Food Frequency Questionnaire (FFQ) and dietary diversity questionnaire recommended by the UN Food and Agriculture Organisation [29]. The antenatal follow-up questionnaire also consists of three components: i) information on services utilization, ii) anthropometric measurement and iii) FFQ and dietary diversity questionnaire. Postnatal follow-up questionnaire consists of two components i) maternal and neonatal services utilization along with morbidity and mortality and ii) new-born anthropometric measurement and child care practices. A focus group discussion (FGD) guide is prepared to collect information on attitudes and beliefs of FCHVs and pregnant women on service utilization and nutrition practices to give an in-depth understanding on the status of dietary diversity and complement some of the quantitative findings.

### Anthropometric measurement

Anthropometric variables: All the anthropometric measurements will be taken on each pregnant women and their subsequent child using standard anthropometric measurement techniques [30].

### Haemoglobin estimation

A total of 2 ml venous blood will be collected and kept in EethyleneDiamine Tetra-acetic Acid (EDTA) vial. Collected EDTA blood will be transferred to the clinical pathology laboratory of Janaki Health Care and Research Centre, Janakpur and Haemoglobin concentration will be estimated by Cyanmethemoglobin method.

### Data collection plan

The structured questionnaire has been piloted using responses from 20 households in the adjacent district. Necessary feedback is received and the amendment has been made in the final questionnaire before baseline data collection. Data will be collected by research assistants who are trained in the tools and techniques of data collection. Anthropometric assessment will be taken by six Female Research Assistants (FRAs) (one FRA per VDC).All measurements will be made three times and the median value will be recorded for analysis. The collection of information on pregnancy, outcomes and its determinants will be made longitudinally at different stages. The methods will employ structured interviews, FGD and anthropometric assessment.

Data will be collected at four chronological points. Baseline information on demographic characteristics, obstetric history, anthropometry, biochemical test, dietary survey and current practices on services utilization will be taken on 4–6 month prior to intervention. The reminders will be the follow-up period as described below;Assessment of pregnant women (services utilization, dietary survey, anthropometry and biochemical test) in the 9th month during intervention (Follow up- I).Data on birth weight will be taken by FRAs preferably within the first hour of the birth (Follow up II).Assessment of mother and child (services utilization, dietary survey and anthropometry including maternal and child morbidity) and satisfaction of the participants at the7th month after intervention (Follow up III).

